#### Focus group I

2.3.1

The aim of this focus group (*n* = 5) was to collect information on past and present dietary habits as well as physical activity and exercise routines. The participants in this focus group were asked to complete a diet journal through the Automated Self-Administered 24-Hour (ASA-24) dietary recall system (74). Participants also completed the Food Frequency Questionnaire (FFQ) to elicit information on how often they consumed different categories of food (75). Current physical activity levels and exercise habits were assessed through the International Physical Activity Questionnaire (IPAQ) (USDA).

#### Focus group II

2.3.2

The purpose of the second focus group (*n* = 10) was to illicit information on participants’ gastronomic preferences and sensitivities, knowledge of nutrition and various ingredients, and motivation to change their current dietary routine. Importantly, this focus group helped to highlight potential challenges in adherence to a dietary structure that may be unique to an early psychosis population. Participants in this group also provided input on their food environments and perceived notions of food availability and affordability within their communities. This food environment information was gleaned through the Appetite and Eating Questionnaires (AEQ) which encompassed several self-report scales: The Short Nutritional Assessment Questionnaire (SNAQ) assessed potential levels of malnutrition (76), the Food Craving Index (FCI) assessed daily cravings for specific foods (77). Additionally, this focus group was asked questions regarding emotional responses to gaining weight, eating certain types of food, and eating customs through the Three-Factor Eating Questionnaire (TEEQ) (78).

Information collected from this focus group also provided insight into an ambiguous and scarcely researched element of life for those living with psychosis: their food environments and the perceived accessibility and affordability of healthy foods in their communities. While previous findings have suggested that individuals living with serious mental illness are particularly vulnerable to food deserts and lack of access to nutritional foods, there is a dearth of culturally competent studies which have aimed to understand one’s perceived food environment, especially for those in the early phases of illness (79). The Nutrition Environment Measures Survey-Perceived (NEMS-P) was utilized to collect information on perceived nutrition environments of participants and assessed community nutrition environment, individual nutrition environment, home food environment, demographics, and shopping behaviors (80).

#### Focus group III and IV

2.3.3

The aim of the third focus group (*n* = 5) was to collect participant feedback on the instructional materials for the DI. This involved participants evaluating individual measures, recipes, and educational handouts given as part of the DI (Figure 2). The fourth focus group (*n* = 5) assessed overall participant satisfaction with the entire DI via the Participant Satisfaction Survey. Adapted scales from Weiner et al. (81) were used to assess the feasibility and acceptability of the intervention materials and the proposed intervention consisting of questions that required the participant to rate on a Likert scale their level of agreement with several statements regarding acceptability, feasibility, accessibility. This modified scale is included in the Supplementary material. Participants will also have the opportunity to provide unstructured qualitative insight into these aspects of the DI and research participation. Findings from these final focus groups provided insight into the readiness of the proposed DI, now further refined through an iterative process, to proceed to the Feasibility Phase. Preliminary results from the Formative phase will be reported elsewhere. Updated recipes were developed by study staff from the Center for Integrative Medicine at UCSD based on feedback from the Formative Phase. These recipes will be employed in the Feasibility Phase and are included in the Supplementary material.

**Figure 2 fig2:**
[figure not shown]
Educational handouts provided to the participant in focus groups 3 and 4.

### Phase III: feasibility phase

2.4

The primary aim of the Feasibility phase is to assess the feasibility and acceptability of the 5-week anti-inflammatory DI developed in the Formative phase among a small FEP cohort (81). A secondary aim is to naturalistically evaluate the impact of the 5-week DI on weight and various other metabolic markers of inflammation as well as on clinical symptoms. The DI’s duration of 5-weeks was both informed by experience within the CIM regarding an appropriate duration to see metabolic changes, as well as input from patients in the Formative Phase of an appropriate timeline for their availability and interest. Meta-analytic findings also demonstrate that short-term dietary interventions (longer than 2 weeks) have been shown to impact gut microbiota (82), and similar reviews have noted that anti-inflammatory dietary interventions longer than 4 weeks may have observable effects on blood-based inflammatory markers (83, 84) A projected sample size of 12 for this phase was proposed *a priori* based on similar feasibility studies within the CIM, and parameters that would be measured in the Feasibility phase were selected based on responses from participants in the Formative phase. Following the Formative phase, study staff from both the UCSD CARE Program and the CIM discussed participants’ qualitative and quantitative feasibility and acceptability ratings for all assessments administered as well as educational materials provided. Study staff then discussed and decided, based on these responses, which assessments and educational materials would be administered in the Feasibility phase and reduced assessments in which there was significant overlap of content or which participants had expressed difficulty completing or understanding (Table 4). Given that the objectives of the proposed study are to assess the feasibility and acceptability of the DI as well as to explore any impact on metabolic outcomes following the DI within an FEP population, healthy control participants will not be included in this pilot study as there is no methodological question proposed in this project regarding applicability or comparability to a healthy control group.

**Table 4 tab4:** Study flow- feasibility phase.

	Assessment	Feasibility phase					
		Baseline (Week 0)	Phone-check-in (Week 1)	Phone-check-in (Week 2)	Clinical evaluation (Week 3)	Phone-check-in (Week 4)	Endpoint (Week 5)
General forms	Demographics	X					
	Informed Consent	X					
	Review of inclusion/exclusion criteria	X					
	Medical & Family History Questionnaire	X					
	Clinical Assessment with MD	X					
Clinical assessment forms	SCID-5	X					X
	PANSS	X					X
	CDSS	X					X
Physical evaluation tools	Anthropometrics	X					X
	Weight	X					X
	Vital Signs	X					X
	Blood Chemistries (insulin, glucose, HgA1C, lipids, liver function test); (1ML)	X					X
	Biomarkers of Inflammation (20ML)	X					X
	Diet Counseling	X	X				
Dietary assessment tools	EAT-26	X					
	ASA-24	X	X		X		X
	FFQ	X					X
	Appetite and Eating Questionnaire Motivation for Change	X					X
	Diet Habits Survey						
	NEMS-P	X					
	Cooking videos		X	X	X	X	
	Diet Education materials		X	X	X	X	
Physical activity assessment form	IPAQ Long	X			X		X
	Health Coaching Telephone	X	X	X	X	X	X
Health coaching forms	Diet Adherence (HC note)		X	X	X	X	X
	Concomitant medications	X	X	X	X	X	X
	Assessment of AEs-Tolerability		X	X	X	X	X
End of treatment SURVEYS	Acceptability						X
	Feasibility						X
	Satisfaction/Perception						X

Given that participants are going to be recruited directly from the UCSD CARE Early Psychosis program, we anticipate retention across the 5-week DI as study staff have regular communication and interaction with patients in the clinic and research setting. If participants withdraw or leave the study at any point during the 5-week DI, this missing data will be incorporated into our holistic understanding of the feasibility and acceptability of the DI. Participants in this study are not randomized and primarily qualitative data is being collected over the course of the DI, therefore typical methods for managing attrition issues and missing data used in clinical trials such as intention to treat (ITT) or last observation carried forward (LOCF) analyses are not necessary. FEP participants recruited to this phase will importantly be different than those who participated in the Formative phase to ensure objective exposure to final DI material. Possible barriers to attrition are also addressed through the modality in which the DI will be delivered; participants will only come into the research center physically for the baseline and endpoint collection of bio-samples, and all clinical assessment appointments and weekly diet-coaching sessions will be held remotely.

### Data analysis, monitoring, and management

2.5

For the clinical and metabolic measures collected in the Feasibility phase (discussed below), a series of exploratory analyses will be used to estimate effect sizes and directionality of changes from pre to post 5-week DI. If basic statistical assumptions are met, the preferred method of analysis will be a one sample paired t-test between baseline and end point measures. If the final data does not meet these assumptions, an alternative Wilcoxon signed-rank will be considered. Pearson’s correlation will be used to analyze the association of average adherence to secondary outcome measures, however if the data appears to be non-parametric, alternative Spearman’s correlations will be considered. For the analysis of feasibility, acceptability and participant satisfaction of the DI, descriptive statistics will be obtained for all variables and the appropriate statistical test will be employed to assess normality and homogeneity of variance.

Per the UCSD Health IRB guidelines, participant data will be collected under de-identified subject IDs. All data will be collected and simultaneously input into a secure REDCap database formulated specifically for this study (87). Clinical assessments, demographic data, and diet coaching materials will all be stored on this secure database. Study staff will have all completed the required Collaborative Institutional Training Initiative (CITI) certification for research in Human Subjects (CITI).

## Anticipated results and outcomes

3

### Adherence to a 5-week anti-inflammatory DI: clinical and metabolic outcomes

3.1

Height, weight, and other markers of obesity and metabolic health will be collected pre and post DI (Table 4). Plasma lipids, fasting glucose, hemoglobin A1C (HgA1C), C-Reactive Protein (CRP), and insulin levels will be collected via blood draw at baseline and week 5. The gut microbiome for each participant will be examined pre and post intervention through the collection of fecal samples at baseline and at endpoint. Based on preexisting fecal sample collection protocols from Sinha et al. (85), samples will be obtained using Fecal Occult Blood Tests (FOBT). Levels of immune-modulating gut species *Lactobacillis* and *Bifidobactirium* will be analyzed using Shotgun metagenomics sequencing (85, 86). During this initial visit, participants will be introduced to study staff and provided with instructional material on the DI as well as a 5–7 day meal plan that will be adjusted with each week of the DI. They will be provided with dried goods that are essential for the DI, and will be given instructions on how to complete questionnaires and will gain access to online instructional cooking material.

After baseline, participants will meet once per week for 5 weeks with study staff and complete questionnaires. During these weekly check-ins, participants will meet with the registered dietician and review weekly adherence to the DI, as well as barriers and facilitators related to adherence. The registered dietician will consult on modifications to the DI as well as review sample recipes with the participant and answer any questions (Supplementary material). Medication adherence and overall health and well-being will be assessed at these visits, and participants will be encouraged to explore the available online resources of cooking videos and recipes to assist them with the DI. After the 5-week DI, participants will complete final biomarker testing and clinical evaluation.

### Feasibility, acceptability, and adherence

3.2

One aim of the Feasibility phase of this DI will be to assess patterns of participant recruitment and retention, participant satisfaction to the DI, and to evaluate the overall feasibility of a 5-week anti-inflammatory DI among FEP cohorts. Adherence to the overall research process will be evaluated based on the number of participants that complete all timepoints of the study. Adherence to the DI will incorporate this measure as well as qualitative weekly adherence to the DI as recorded by the registered dieticians in the weekly coaching sessions. At the end of the 5-week DI, feasibility of the DI will be informed by participant self-report (81, 89). Subjects will also be asked to complete the Research Participant’s Perception Survey-UP to provide feedback into their overall experiences as a research participant in this study (89). This phase will also elucidate the feasibility of collecting and monitoring naturalistic changes in certain biomarkers that can be used to measure metabolic health in early psychosis populations, which is an area of significant interest in the study of inflammation across psychiatric disorders. Similarly, psychiatric symptoms will be evaluated pre-and-post DI as an exploratory aim. Any changes in symptoms observed following adherence to the DI will inform the relevance of monitoring psychiatric symptoms in this context.

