## Methods

2

Participants in this study will be recruited from the University of California San Diego Cognitive Assessment and Risk Evaluation (CARE) program, an early psychosis clinic and research program. Recruited participants will complete an informed consent or assent to participate in a research study in accordance with the University of California San Diego Health Institutional Review Board (IRB). The development and implementation of this novel DI will be based on expert input from both the CARE program as well as the University of California San Diego Center for Integrative Medicine (CIM), a leading institution in nutrition research. This study will be conducted in three distinct phases following a similar process described by Bustamante et al. (46) who studied anti-inflammatory DI in rheumatoid arthritis. The first phase, the Development phase, involved active collaboration between researchers and clinicians to develop the DI. The second, or Formative, phase involves the recruitment and formation of focus groups (*N* = 25) with the aim of collecting qualitative interviews regarding FEP participants’ and their families’ perspectives on diet, nutrition, and health to refine the final DI. The third, or Feasibility, phase will pilot the DI within one group of FEP participants (*N* = 12) utilizing a pre/post design to assess the feasibility and acceptability of the DI. Sample sizes for each group were predetermined based on anticipated recruitment feasibility/availability of patients within the UCSD CARE program. In the Feasibility phase, researchers will also investigate the feasibility of collecting clinical outcome measures as well as metabolic markers such as weight and levels of biomarkers of inflammation. The following description of the proposed feasibility protocol will adhere to the Standard Protocol Items: Recommendations for Interventional Trials (SPIRIT) guidelines in which specific hypotheses and aims are stated (above), inclusion/exclusion criteria, methodology and relevant measures, location of study activities, rationale for sample size, timeline of the proposed study, as well as data management and statistical analyses (62). Per the National Institutes of Health Final Rule regarding clinical trial registration (FDAAA 801), the proposed feasibility study protocol does not meet the criteria for an applicable clinical trial (ACT) and was not pre-registered (63).

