### Limitations

4.1

The proposed study has several potential limitations. Generalizability of findings from this study is limited by the singular site in which it was conducted, and findings are only representative of the participants who completed this DI and are not broadly applicable to all FEP contexts. Future clinical studies that may implement this DI, if feasibility and acceptability are determined in the proposed study, can include direct comparisons between FEP control groups receiving standard of care treatment to those receiving anti-inflammatory DI adjunctive to standard of care. These studies should ensure representation from a diverse range of FEP individuals, larger sample sizes for statistical power, as well as inclusion of multiple clinical sites from varying geographic regions. Future studies may also explore longitudinal differences in response to this DI; the duration of the proposed DI was determined *a priori* based on expertise among research staff, patient perspectives, and existing literature to be reflective of a relatively limited time-window. Findings regarding the feasibility of this adherence to this short-term DI do not speak to the long term sustainability of this intervention in this population. Importantly however, findings regarding the “appropriate” or “recommended” length or sustainability of anti-inflammatory dietary interventions are mixed (46, 49, 52).

Importantly, while evidence of the role of inflammation in the pathophysiology of psychosis is promising and highlights important biological processes associated with psychosis, it is critical to underscore that this research is in its infancy especially in the context of early-course psychosis. The aim of this study is solely to provide the preliminary blueprint of a DI for early psychosis that is formed and refined using data and feedback collected from participants, with the Feasibility phase assessing the feasibility and acceptability of the DI along with metabolic and inflammatory biomarker assessments as target endpoints. Changes in metabolic and psychiatric health in the Feasibility phase may provide insight into the potential clinical treatment model, however future clinical trials would be required to evaluate its utility beyond the present sample.

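### The acceptability, feasibility and satisfaction surveys are scheduled only at Week 5, so participants who stop early give no rating and the ratings are at risk of upward survivor bias

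*Protocol article*

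**What the plan says.** Section 2.4 of the protocol article sets the aim: "The primary aim of the Feasibility phase is to assess the feasibility and acceptability of the 5-week anti-inflammatory DI". On size it says "A projected sample size of 12 for this phase was proposed", and Methods (section 2) adds "Sample sizes for each group were predetermined based on anticipated recruitment feasibility/availability of patients within the UCSD CARE program".

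Table 4 groups three instruments (Acceptability, Feasibility, Satisfaction/Perception) under "End of treatment SURVEYS". Each has one mark, in the Endpoint (Week 5) column. Section 3.2 gives the same timing: "At the end of the 5-week DI, feasibility of the DI will be informed by participant self-report". Section 2.3.3 describes the adapted feasibility and acceptability scales as Likert ratings, and section 3.2 cites the same source. Section 2.5 plans descriptive statistics for feasibility, acceptability and satisfaction.

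On dropout, section 2.4 says "we anticipate retention across the 5-week DI" and gives no rate. If someone does withdraw, "this missing data will be incorporated into our holistic understanding of the feasibility and acceptability of the DI". The same paragraph calls intention-to-treat and last-observation-carried-forward analyses unnecessary. Section 4.1 states as a limitation that "findings are only representative of the participants who completed this DI".

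**The concern.** A participant who finds the diet unpalatable or unworkable and stops in Week 2 or 3 is the person whose acceptability rating would be most informative. Under the stated schedule that person is never asked. Descriptive statistics on Week 5 forms then describe only those who reached Week 5, and a withdrawal cannot be folded into an overall judgement of acceptability as a rating, because no rating exists.

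This bears on the primary aim. Section 4.1 makes later controlled studies conditional on feasibility and acceptability being established here. Favourable ratings from completers alone could support that step for a diet that some enrolled participants could not follow.

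**Working it through.** **Step 1. What is recorded for someone who stops early?**

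| Source of information | Where stated | Timing | Available for a leaver? |
|---|---|---|---|
| Recruitment and retention patterns; number completing all timepoints | 3.2 | whole study | Yes |
| Dietician's adherence notes | 3.2, Table 4 | Weeks 1 to 5 | Up to leaving |
| Barriers and facilitators | 3.1 | weekly check-ins | Up to leaving |
| Adverse events and tolerability | Table 4 | Weeks 1 to 5 | Up to leaving |
| Acceptability, Feasibility, Satisfaction/Perception surveys | 3.2, Table 4 | Week 5 only | No |

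The gap is confined to the last row. Because each survey is taken once, an imputation rule such as carrying the last observation forward would have nothing to carry.

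**Step 2. Inputs for sizing the gap.** N = 12 is from section 2.4. It rests on recruitment availability and similar studies, with no alpha, power, effect size or SD, so there is no calculation to reproduce. The number lost before Week 5 (m), the rating gap between completers and leavers (g), and the number of favourable completers (x) are not in the article. All three are assumptions below, as is splitting a Likert scale into favourable and unfavourable.

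**Step 3. Shift in a mean rating.** The mean over all 12 is [(12 − m) × completer mean + m × leaver mean] / 12. Subtracting this from the completer mean gives

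shift = (m / 12) × g, where g = completer mean − leaver mean.

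| m lost | g = −0.5 | g = 0 | g = 1 | g = 2 |
|---|---|---|---|---|
| 0 | 0 | 0 | 0 | 0 |
| 1 | −0.04 | 0 | +0.08 | +0.17 |
| 2 | −0.08 | 0 | +0.17 | +0.33 |
| 3 | −0.125 | 0 | +0.25 | +0.50 |
| 4 | −0.17 | 0 | +0.33 | +0.67 |

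For example, with m = 3 and g = 1: (3/12) × 1 = 0.25 Likert points. The shift is upward only if leavers would have rated lower than completers.

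**Step 4. Bounds on a proportion favourable.** With x favourable among 12 − m completers, the value for all enrolled lies between x/12 (every leaver unfavourable) and (x + m)/12 (every leaver favourable).

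| m lost | Completers favourable | Survey shows | All 12: lowest | All 12: highest |
|---|---|---|---|---|
| 0 | 12 of 12 | 100% | 12/12 = 100% | 12/12 = 100% |
| 1 | 11 of 11 | 100% | 11/12 = 92% | 12/12 = 100% |
| 2 | 8 of 10 | 80% | 8/12 = 67% | 10/12 = 83% |
| 3 | 9 of 9 | 100% | 9/12 = 75% | 12/12 = 100% |
| 3 | 8 of 9 | 89% | 8/12 = 67% | 11/12 = 92% |
| 4 | 8 of 8 | 100% | 8/12 = 67% | 12/12 = 100% |

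The interval is m/12 wide, so each unrated leaver adds 1/12 = 8.3 percentage points of uncertainty. Each leaver who completes the survey at exit removes the same amount.

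**The case against.** The strongest case against runs as follows. Feasibility in section 3.2 is more than the end ratings: a leaver lowers the completion count and leaves adherence, barrier and tolerability notes behind. Section 2.4 commits to using withdrawals in judging feasibility and acceptability, and section 4.1 openly limits the findings to completers. Retention is expected for stated reasons (regular clinic contact, mostly remote visits). This is a 12-person single-arm pilot with descriptive outcomes and no numerical success threshold. A rule for scoring withdrawals may stand in a fuller protocol or analysis plan.

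Most of this stands, and it rules out three stronger readings that a reader might infer.

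- *That the whole primary outcome is measured only in those who stay.* The first four rows of the Step 1 table show otherwise.
- *That the ratings will be biased upward.* This needs both dropout and lower ratings among leavers. The article establishes neither, and people may leave for reasons unrelated to the diet.
- *That the plan ignores withdrawals.* It addresses them, but only as a general intention.

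What the objection does not remove is the survey schedule. That is stated here, in Table 4 and in section 3.2, and is not a detail left to another document. The commitment to take withdrawals into account cannot recover ratings that were never collected, and the limitation in section 4.1 discloses the gap without closing it. Nor do the reasons given for setting aside intention-to-treat (no randomisation, mainly qualitative data) settle who belongs in the denominator of a single-arm rating.

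**Conclusion.** The point holds for the self-rated part of the primary aim. As scheduled, acceptability, feasibility and satisfaction ratings come from completers only, and they are at risk of upward survivor bias if dissatisfied participants leave. The other feasibility measures capture leavers but do not substitute for their ratings.

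The size cannot be fixed from the article, because it rests on an assumed number of leavers and an assumed rating gap. It is zero without dropout. With 3 of 12 lost and all completers favourable, the survey reads 100% and the all-enrolled value is anywhere from 75% to 100%.

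It would also go too far to score every leaver as unfavourable in the main result. That would risk a downward bias by counting unrelated departures as rejection of the diet, and it would merge retention with attitude, which section 3.2 treats as separate matters. The point is a cheap and worthwhile improvement and does not invalidate the study.

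**What to change.** 1. In Table 4, change the timing of the Acceptability, Feasibility and Satisfaction/Perception surveys from Week 5 to Week 5 or early exit, and align the wording of section 3.2.
2. Give the surveys by phone or online when a participant stops the diet intervention, and record the reason for stopping.
3. In section 2.5, state that ratings are reported with the number contributing out of all enrolled, beside retention.
4. Add one sensitivity bound, not the main figure, in which leavers without a survey count as unfavourable.

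The cost is a change to three table rows, a sentence or two of text, and a short remote survey for the few who leave. The reported figure may be less favourable. The abstract describes this phase as under way, so the change is best made promptly: a rating not taken at exit may not be obtainable later.
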